## Abstract

**Background:**

People with mental illness have a reduced life expectancy compared to the general population. Despite the increasing evidence for the efficacy of lifestyle interventions there is little change in routine clinical care. This discrepancy is often referred to as the implementation gap and has caused a need for effectiveness and implementation research in real-world settings. Our study assesses the effectiveness and implementation of a multidisciplinary lifestyle focused approach in the treatment of inpatients with mental illness (MULTI +).

**Methods:**

An open cohort stepped wedge cluster randomized trial in inpatients psychiatric wards of GGz Centraal, the Netherlands. The wards are divided into three clusters based on geographical region. These clusters are randomly allocated to one of the three pre-defined steps to integrate MULTI + . MULTI + can be tailored to fit individual psychiatric wards and includes 10 core components aimed at improving lifestyle factors. The primary outcome is to investigate the difference in the mean QRISK3 score of patients receiving MULTI + compared to patients receiving TAU. Secondary outcomes include somatic and mental health outcomes, lifestyle factors, and implementation factors. Findings will be analysed using mixed model analyses.

**Discussion:**

The MULTI + study is the first large-scale study evaluating the long-term effects of a multidisciplinary, multicomponent approach aimed at improving lifestyle factors in routine inpatient mental health care. A limitation of this study is the risk of missing data due to the large-scale, real-world setting of this study. Furthermore, implementation monitoring and external events that may influence outcomes could be difficult to account for. Strengths of this study are the focus on effectiveness as well as implementation and the inclusion of both patient and health care professionals’ perspectives. Effectiveness studies in routine clinical care can advance our knowledge on lifestyle interventions in real-world settings.

**Trial registration:**

ClinicalTrials.gov registration. Identifier: NCT04922749. Retrospectively registered 3th of June 2021.

**Supplementary Information:**

The online version contains supplementary material available at 10.1186/s12888-022-03801-w.

## Background

People with mental illness (MI) have a reduced life expectancy compared to the general population, mostly attributable to somatic diseases caused by poor physical health [1, 2]. Irrespective of their diagnosis, people with MI have 1.4–2 times higher risk of cardiometabolic diseases (e.g. cardiovascular disease (CVD) and diabetes), many of which can potentially be avoided [3–5]. Modifiable lifestyle factors such as physical activity (PA), diet, sleep and smoking behaviour have been increasingly associated with the onset of somatic diseases in people with MI [3, 5–8]. Adverse health behaviours are prevalent in people with MI and the resulting poor physical health is often exacerbated by the adverse effects of psychotropic medication [9, 10]. Hence, it is important to stimulate healthy lifestyle behaviours in people with MI.

There is increasing clinical and scientific evidence for the efficacy of interventions targeting lifestyle factors [6]. A series of reviews and meta-analyses that analysed interventions aimed at improving PA [11, 12], nutrition and diet [13, 14], sleep [15, 16], and smoking cessation [17] have shown favourable results on cardiometabolic health, psychosocial functioning and quality of life. In addition to this, reductions in MI-related symptoms such as negative symptoms, depression and psychotic symptoms were found. Despite this overwhelming evidence demonstrating the efficacy of interventions aimed at improving lifestyle factors, there have not been many structural changes in routine clinical care for people with MI [5, 18–21].

Implementing and sustaining interventions is an intricate process, and multiple factors can hinder the translation of evidence into practice [20, 22, 23]. For example, efficacy research mostly uses a randomized-controlled trial (RCT) design which can often not be translated linearly into routine clinical care, resulting in diminished effects [24, 25]. Moreover, trials often do not pass research stages, or are less likely to be sustained [22]. Pragmatic clinical trials could promote the implementation and sustainability into routine clinical care because they better reflect real-world conditions [26]. In addition, implementation factors, such as organisational culture and financial sustainment, can complicate the uptake and continuation of lifestyle interventions [27]. Studies investigating implementation factors are scarce, whilst several publications highlight their importance [6, 20, 28, 29]. Consequently, the focus of the present research is on the implementation gap (*i.e. how to make it work)*, rather than a knowledge gap (*i.e. does it work?)* [20].

The most efficacious lifestyle interventions are delivered by qualified health care professionals (HCPs) and target multiple lifestyle factors simultaneously [5, 29, 30]. However, research on such multidisciplinary, multicomponent lifestyle interventions is scarce and little is known about long-term effects and sustainability. Moreover, most research is conducted in outpatient settings. Further research in inpatient settings is especially important considering the high illness severity and comorbidity in this patient population [31].

Deenik and colleagues [30] previously evaluated a multidisciplinary, multicomponent approach (called MULTI) aimed at a holistic lifestyle change in a real-world inpatient setting for people with severe mental illness (SMI). They found positive changes in both somatic and mental health after 18 months compared to usual care, such as improvements in metabolic risk factors, psychosocial functioning and a reduction in the use of psychotropic medication [32, 33]. The authors urged to confirm and complement findings in scaled-up studies and made several suggestions for improvement of the approach and pragmatic research of implementation [30]. In line with these recommendations, MULTI has been further developed into MULTI + and will now be implemented on a larger scale. We aim to investigate the effectiveness and implementation of this multidisciplinary lifestyle focused approach in the treatment of inpatients with mental illness (MULTI +).

## Methods

### Study design and setting

This study is an open cohort stepped wedge cluster randomized trial conducted at all inpatient wards of the specialist mental healthcare organisation GGz Centraal (the Netherlands) [34]. The organisation will implement MULTI + semi-annually in three geographical regions (clusters). Wards are almost equally distributed per cluster, covering a total of ~ 830 places of residence in which ~ 2000 patients are treated annually (Table 1). This gradual implementation intends that all clusters are exposed to MULTI + at the end of this trial. Each step includes a one-month transitional phase to prepare the cluster for the implementation of MULTI + . This trial takes 18 months to complete.

**Table 1 Tab1:** *Places of residence divided in three clusters*

**Cluster**	**Wards (n)**	**Places of residence (n)**
1	15	~ 300
2	14	~ 300
3	15	~ 230

In line with the regional implementation, cluster-level randomisation is used. Individual-level randomisation is not possible because patients cohabit in groups within wards. Moreover, cluster-level randomisation minimizes the risk for contamination between HCPs working in multiple wards or different geographical clusters. Due to high patient turnover the patient population may differ at each measurement and individual follow-up for long-term evaluation is not feasible after discharge.

Measurements are obtained at the same time in all clusters at baseline (T0), after six months (T1), after twelve months (T2) and after eighteen months (T3). Measurements take approximately three months to complete (Fig. 1).

**Fig. 1 Fig1:**
[figure not shown]
Open cohort stepped wedge cluster randomized trial in inpatient psychiatric wards in three clusters, demarcated by the dates of implementation of MULTI + . Measurements are obtained semi-annually

### Eligibility criteria

Patients aged ≥ 16 years who receive care at the inpatient psychiatric wards of GGz Centraal are eligible to participate in the study. Patients are not eligible to participate when they have limited knowledge or understanding of the Dutch language, or if their psychiatric or physical condition hinders informed consent at the discretion of the relevant physician, nurses, or researcher.

### Intervention

MULTI + is a multidisciplinary, multicomponent intervention which aims to improve lifestyle factors through a holistic approach. MULTI + focuses on 10 core components (i.e. the elements and activities that are necessary to achieve desired outcomes) [35], based on previous research and recommendations (Table 2) [5, 14, 30]. MULTI + is embedded in the long-term policy of the mental health care organisation, creating a support base and resources to facilitate implementation at all organisational levels. The implementation of the core components is co-designed with, and tailored to the ward and patient population, because of the large heterogeneity in patient characteristics and varying access to facilities and staffing.

**Table 2 Tab2:** *10 core components of MULTI + and application into routine clinical care*

Core components of MULTI + ^a^	Application of core components
Routine daily structure and sleep	Wards offer a routine structure in a day-to-day program which includes standard mealtimes, sports-related activities, work-related activities, psychoeducation, and skills training. HCPs pay attention to the circadian rhythm and sleep hygiene of patients. It is intended that patients participate in at least two activities per day, such as walking in the morning and psychoeducation in the afternoon. HCPs motivate patients to engage in activities
Physical activity	Decreasing sedentary behaviour and increasing PA with the credo: “doing some physical activity is better than doing none” as a starting point. The eventual aim is to meet the (inter)national physical activity guidelines of ≥ 150 min of moderate-intensity PA every week, spread over several days [36, 37]. Additionally, patients engage in muscle- and bone-strengthening activities at least twice a week. Elderly patients combine these with balance exercises
Attention to nutrition and eating habits	Attention for the nutritional value and composition of meals and snacks in compliance with the Dutch national guidelines [38], as well as eating habits such as mealtimes and mindful eating. There are (preventive) consultations with dietitians on (clinical) indication of patients or HCPs
Substance use	Smoking cessation is encouraged in both HCPs and patients, and patients are supported by smoking interventions on (clinical) indication of patients or HPCs. For other substance use, patients are referred to addiction specialists
Multidisciplinary approach	Various disciplines are involved in the guidance of a single patient based on the patients’ needs and wishes, such as practitioners, nurses, exercise professionals and dietitians. These HCPs discuss the progress and compliance of individual patients in multidisciplinary consultations led by the chief physicians
Skills training	Daily living skills training and activities for patients, such as making a grocery list, shopping and cooking are embedded in the day-to-day program. Evidence-based behavioural techniques such as goal setting, planning and use of rewards are applied
Psychoeducation	Psychoeducation for patients, such as information about side-effects of medication, oral hygiene, sleep hygiene or nutrition is offered and embedded in the day-to-day program
Critical review of obesogenic environment and existing policies	HCPs examine the (obesogenic) environment and existing policies such as the availability of (un)healthy food and beverages, the use of personal transport and designated smoking areas, and adjust these if necessary. Behavioural change techniques such as choice-architecture and nudging are used
Active participation of HCPs	It is intended that at least one HCP participates in activities of the day-to-day program. HCPs do not engage in adverse health behaviours around patients, such as smoking and unhealthy eating as they have an exemplary function. HCPs motivate patients to improve their lifestyle factors
Training of HCPs	HCPs make use of the available educational resources and follow courses and training such as motivational interviewing or moral deliberation. These activities can support HCPs in motivating and educating patients, and facilitates awareness and culture change

*HCPs* Healthcare Professionals, *PA* Physical Activity

^a^Cross-compliance for implementation of core elements: culture change, peer support, co-designing, tailoring

MULTI + is implemented gradually in every cluster at ward level between November 2020 and November 2021. The explicit aim is the integration into routine clinical care instead of MULTI + being a temporary intervention. The chief physicians supervise the implementation. Four to six months before the start of implementation we approach the chief physicians to discuss the practical start with, and integration of the core components.

Because the organizational structure differs between clusters and wards, the practical dissemination and implementation of the core components of MULTI + may be adjusted where needed to promote sustainability. Nonetheless, every ward should have a multicomponent approach and have multidisciplinary consultations with qualified HCPs of relevant disciplines, such as practitioners, nurses, movement therapists and dietitians. HCPs develop active day-to-day programs in multidisciplinary work sessions tailored to their respective psychiatric wards. This day-to-day program includes various activities in accordance with the core components.

It is intended that patients participate in at least two activities per day to decrease sedentary behaviour. HCPs actively participate in these activities. Attending activities together contributes to joint responsibility and group feeling, increases peer support among patients, and facilitates culture change. When possible, patients are involved in designing the activities in the day-to-day program by fitting the activities to their capabilities and interests, to increase their intrinsic motivation. Compliance of patients with the intervention is discussed in multidisciplinary consultation among HCPs and extra support to the patient is provided when needed. The possibilities for co-design and tailoring makes MULTI + uniquely applicable to various forms of daily clinical care.

To establish long-term sustainability, an implementation team is formed to evaluate and safeguard ongoing improvement of MULTI + . This team consists of a senior researcher, a project leader and two junior researchers, and facilitates key activities in the implementation, improvement and continuation of MULTI + [39]. In collaboration with the implementation team, educational resources for HCPs and patients about lifestyle factors are developed to increase knowledge and enhance skills and capabilities. These resources are distributed using company-specific communication channels (such as internal webpages, e-mail, and teams’ pages), presentations, podcasts, e-learning modules, and webinars. The implementation team works in close collaboration with key stakeholders such as the board of directors, head physicians, nurse advisory board, the client association, and representatives of the family board. Research has shown that implementation teams can guide implementation and ensure faster, more successful outcomes [39].

### Treatment as usual (TAU)

TAU consists of pharmacological treatment, psychotherapy, and a less structured day-to-day program. Concomitant forms of care may be provided during the study.

### Data collection and management

Data is obtained from routine screening (from electronic patient files according to the organisational data protocol) and questionnaires. Questionnaire data, including demographics, is collected with Castor EDC [40]. This is a cloud-based electronic research data management platform for the secure collection and management of data. Questionnaires for HCPs are conducted through online surveys. We administer the questionnaires for patients through semi-structured interviews, because inpatients with MI often experience cognitive deficits, which can lead to impaired concentration, memory deficits and poor understanding of questions [41, 42]. Semi-structured interviews allow for the clarification of questions when needed. Due to illness severity and cognitive deficits, not all patients may be able to complete all questionnaires. Patients are included in this study if they complete at least one questionnaire. Conducting all questionnaires takes 45–60 min per patient, which can be completed in multiple appointments if necessary. A researcher or trained research assistant conducts the semi-structured interview. Training consists of a presentation of the research protocol and instructions on each questionnaire followed by role-play. To increase reliability, researchers follow an interview protocol. Weekly meetings are organized with the research team to discuss possible ambiguous answers.

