#### Routine screening data

Routine screening data on somatic health, psychosocial functioning, substance use, medication use and PA is collected semi-annually in patients by trained HCPs.

Data on somatic health is used to calculate the QRISK3 score (i.e. HDL cholesterol, blood pressure, and BMI as calculated by dividing weight in kg by height in m^2^). Additionally, fasting glucose (mg/dL), triglycerides (mg/dL), weight (kg) and waist circumference are measured. Weight and waist circumference is measured to the first decimal (0.1 kg/cm) under the clothes at the level of the umbilicus (with the patient standing).

The Health of the Nations Outcomes Scale (HoNOS) is used to assess psychosocial functioning. The majority of patients will be measured with the HoNOS-12 [44]. The HoNOS 65 + [45] is used for ages 65 and above. The HoNOS-12 and HoNOS 65 + each have 12 items divided into four subscales.

Data on substance use is collected through routine questions about smoking (yes/no/stopped, if yes or stopped, how much on average; packyears are calculated), alcohol use (glasses per day, on average) and use of (soft)drugs (yes/no).

Medication related to cardiovascular health and diabetes, and psychotropic medication will be collected and converted into Defined Daily Dose (DDD) according the Anatomical Therapeutic Chemical Classification System from the World Health Organization (WHO) [46].

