### Research procedures

#### Recruitment

The implementation team informs the HCPs about the measurement procedures. Patients are informed about the study through HCPs and members of the implementation team (see Table 3 for participant timeline). Promotion materials will be used (such as videos, flyers and posters) to give information about the study.

**Table 3 Tab3:** *Participant timeline*

Parameters		Time of Measurement			
		T0 (baseline)	T1 (six months)	T2 (twelve months)	T3 (eighteen months)
Informed consent^a^	PT & HCPs	x			
Demographics^a^	PT & HCPs	x			
Routine screening data^b^	EPR	x	x	x	x
Semi-structured interviews	PT	x	x	x	x
Online surveys	HCPs	x	x	x	x
Process evaluation	ongoing evaluation				
Adverse events					
Costs					

*PT* Patient, *HCPs* Health Care Professionals, *EPR* Electronic Patient Record

^a^Or at first enrolment in the study

^b^Data from routine screening is extracted from the EPR

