The study protocol should be viewed considering several limitations. A first limitation is the risk of missing data. For example, not all patients may be able to complete all questionnaires due to illness severity and cognitive deficits. Therefore, semi-structured interviews will be used to allow for more flexibility and clarification. Another reason for missing data could be patients refusing the administration of the routine screening. Moreover, some routine measurements are only assessed on clinical indication, and will not be present for each patient.

Another limitation is that implementation monitoring could be a challenge because of the large-scale, real-world conditions of the study. Furthermore, external events and organisation-wide changes may impact the effectiveness and implementation of MULTI + due to the non-controlled environment and may be difficult to account for.

Strengths of this study are that MULTI + allows for pragmatic implementation in real-world settings through co-design and tailoring of the 10 core components. We expect that this approach will increase long-term sustainability and can serve as a potential blueprint. Additionally, studying implementation factors will expand our knowledge on how to overcome the implementation gap and successfully implement a lifestyle intervention. Furthermore, we research a broad spectrum of both physical and mental health outcomes in inpatients with MI. This dual research focus on both implementation factors and health outcomes will expand our knowledge on the possible influences these factors have on one another. Ultimately, we aim to improve routine clinical care for inpatients with mental illness.

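### The one-questionnaire inclusion rule conflicts with the wider population described for the primary analysis and, read literally, excludes consenting patients who have QRISK3 data

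*Protocol article*

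**What the plan says.** The inclusion rule stands in the Protocol article under Data collection and management: "Patients are included in this study if they complete at least one questionnaire". The same paragraph explains why some interviews will be incomplete: "Due to illness severity and cognitive deficits, not all patients may be able to complete all questionnaires".

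The primary outcome takes another route. Under Routine screening data: "Data on somatic health is used to calculate the QRISK3 score", with HDL cholesterol, blood pressure and BMI named. The same section says who collects them: "Routine screening data on somatic health, psychosocial functioning, substance use, medication use and PA is collected semi-annually in patients by trained HCPs". A footnote to the participant timeline (Table 3) adds: "Data from routine screening is extracted from the EPR".

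Eligibility criteria lists age, inpatient care, command of Dutch and capacity to consent, and nothing about questionnaires. Statistical analyses describes the primary analysis as covering the QRISK3 of those treated in each cluster-intervention period, with a minimum exposure of 10 days. The Discussion adds that patients under 25 leave the QRISK3 analysis. None of these places repeats the questionnaire rule or waives it.

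**The concern.** The rule governs entry to the whole study, not only to the questionnaire outcomes. It makes an interview the gate to a primary outcome whose named somatic inputs are collected by ward staff without an interview. The reason given for not completing questionnaires is illness severity, which is related to prognosis.

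MULTI+ aims to change daily structure, motivation and mental health, so the share of patients who manage a questionnaire could differ between conditions. If it does, the two conditions are compared on differently selected patients. Usable primary-outcome data would also be discarded, and readers could not tell which population the primary result describes.

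**Working it through.** **1. The sections side by side.** Take a patient aged 25 or over who consents, is exposed for at least 10 days, has HDL, blood pressure and BMI in the record, and completes no questionnaire.

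| Section | Is this patient in? |
|---|---|
| Eligibility criteria | Yes; no questionnaire condition |
| Data collection and management | No; at least one questionnaire is required |
| Statistical analyses | Yes; treated in the period, exposure met |
| Discussion (age limit for QRISK3) | Yes |

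The article gives two answers for the same patient.

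**2. Timing.** Clusters, not patients, are randomised: "These clusters are randomly allocated to one of the three pre-defined steps". Consent and demographics are taken at T0, with the Table 3 footnote "Or at first enrolment in the study", so patients also enter at T1, T2 and T3. For these patients the questionnaire condition is met after clusters were allocated. For T0 the order is unknown, because no randomisation date is given.

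**3. Can the planned analysis repair it?** Multiple imputation fills gaps for included patients; a patient never included has no record to impute. The model adjusts for age, diagnostic subgroup and illness severity. This removes part of any selection on severity, but not selection on other drivers of completion.

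**4. Sample size.** The plan's own figure is 846 patients.
- Two proportions, 16.3% against 32%, two-sided 5%, 80% power, with continuity correction: 128 per arm, 256 in total. Then 256 × 1.1 = 281.6, rounded up to 282, and 282 × 3 = 846. This matches, but it does not use the stated correlation of 0.1, and the article does not name its formula.
- A Hussey-Hughes stepped-wedge calculation with that correlation needs 62 per cluster-period: 62 × 12 = 744, and 744 / 0.9 = 827, within 3% of 846.

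The target is 846 / 2000 = 42.3% of the stated annual turnover. It stays reachable under the rule if about that share consents and completes a questionnaire. The point does not change 846.

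**5. What the bias depends on.** Let c be the share completing at least one questionnaire, and D the amount by which non-completers exceed completers on logit QRISK3, in SD units and equal in both conditions. With no true effect and an overall mean of 0, the completers' mean is −(1 − c)D. The spurious difference, MULTI+ minus TAU, is

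−(1 − c_MULTI+)D + (1 − c_TAU)D = (c_MULTI+ − c_TAU) × D.

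The article gives neither c nor D. Purely assumed values show how it behaves:

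| c_TAU | c_MULTI+ | D = 0.2 | D = 0.5 |
|---|---|---|---|
| 0.6 | 0.6 | 0.00 | 0.00 |
| 0.6 | 0.7 | 0.02 | 0.05 |
| 0.6 | 0.8 | 0.04 | 0.10 |

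Only the difference in completion matters, and the sign follows the signs of that difference and of D. The table ignores the planned covariate adjustment. It illustrates the mechanism and does not estimate this trial's bias.

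**The case against.** The strongest reply is that the sentence is lenient. It follows directly on the remark that not everyone can finish every instrument, so it may only mean that partial completers are kept. The Discussion treats the same problem as missing data rather than exclusion: "not all patients may be able to complete all questionnaires due to illness severity and cognitive deficits". Sample size justifies its 10% dropout by metabolic factors being measured routinely, which also suggests a wider primary population. This reading is possible. It does not settle the matter, because the sentence as written still excludes those who complete none, and nothing exempts the primary analysis.

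Several stronger readings are tempting, and the article does not support them:
- *Patients are in fact being dropped from the primary analysis.* This holds only if the rule is applied literally; Statistical analyses may be meant more widely.
- *QRISK3 needs no interview at all.* The article does not give the source of every input. Demographics are collected with the questionnaire data, and family history, named in the Discussion as a risk factor, is not in the routine screening list.
- *The rule removes the most severely ill.* Those whose condition prevents consent are already ineligible. The group at issue is consenters who complete none of several instruments, some with only five items, despite interviewer help, repeat appointments and ward-staff support. It is probably small.
- *Completion is judged unblinded.* This is plausible, since the intervention is at ward level and researchers sit on the implementation team, but the article does not state it.

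**Conclusion.** The point holds as a conflict between sections with a selection risk attached. One section fixes an inclusion condition that the primary outcome's named somatic inputs do not need and that the eligibility and analysis sections do not contain. Applied literally, it excludes consenting patients with QRISK3 data on a condition tied to illness severity, met after allocation for T1 to T3 enrolments, and beyond the reach of multiple imputation.

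Its size cannot be stated from the article. The number affected is not given and may be small. The bias is zero if completion is equal across conditions and non-completers differ from completers to the same degree in both. Planned adjustment for severity would reduce what remains. The required sample size is not in question.

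**What to change.** Reconcile Eligibility criteria, Data collection and management, and Statistical analyses:

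- Define the primary analysis set as all consenting eligible patients who meet the existing age limit for QRISK3 and the 10-day minimum exposure, whether or not a questionnaire was completed. Handle missing QRISK3 inputs by the planned multiple imputation.
- Apply the one-questionnaire condition to questionnaire-based outcomes only. The article already uses outcome-specific populations: patients under 25 stay in for secondary outcomes, and the quality-of-life part of the cost analysis uses those who answered.
- Report questionnaire completion by condition and period, so that readers can judge any differential selection.

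The set should not be narrowed to consenters with routine screening data. The Discussion says patients may refuse screening and that some measures are taken only on clinical indication. Such a limit would add another selection after allocation and would conflict with the planned imputation.

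The cost is a few sentences and no extra visits. There will be slightly more missing data where covariates or QRISK3 inputs are collected at interview. Informed consent mentions use of personal data without naming record extraction, so the sponsor should confirm that consent covers it for these patients. Selection at the consent step itself is not changed.
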